
|                      |                                                                                                                                                                                                                                                                                                                                                                                                                                                                                                                                                                                                                                                                                                                                                                                                                                  |
|----------------------|----------------------------------------------------------------------------------------------------------------------------------------------------------------------------------------------------------------------------------------------------------------------------------------------------------------------------------------------------------------------------------------------------------------------------------------------------------------------------------------------------------------------------------------------------------------------------------------------------------------------------------------------------------------------------------------------------------------------------------------------------------------------------------------------------------------------------------|
| Objective(s): | 
This study compares under controlled conditions if different flow rates affect apnoea time after induction of anaesthesia and how CO2 clearance is influenced. Furthermore, this study enables to quantify the effects of increased pCO2 on cerebral perfusion.
 
Our primary hypothesis states that any of the three intervention is non-inferior to HFNCT regarding clearance of CO2 (ventilatory effect).
                                                                                                                                                                                                                                                                                                                                                                        |

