## 10. STATISTICAL METHODS

### 10.1 Hypothesis

Null hypothesis: The difference of the mean increase of  $p_{tc}CO_2$  between any of the three intervention groups and the control group is at least 0.3 mmHg/min, the control group being lower.

Primary hypothesis: the difference of the mean increase of  $p_{tc}CO_2$  between the groups is less than 0.3 mmHg/min (non-inferior margin), one-sided testing. This hypothesis was based on a small clinical pilot study that showed no differences regardless of flowrate or mouth opening (jaw-thrust vs. laryngoscopy).

Secondary outcome hypothesis: The number of patients not tolerating the apnoea time of 15 minutes is not significantly higher in any of the three intervention groups.

Secondary outcome hypothesis: no significant changes in vital parameters such as cerebral perfusion will be recorded.

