### 10.2 Determination of Sample Size

We assumed that with maximal flow of 70L O2/min and maximal mouth opening, there would be the least increase of  $p_{tc}CO_2$ /min. Patel et al. showed an increase of only 1.13mmHg using this technique [2]. However, this was  $etCO_2$  instead of  $p_{tc}CO_2$ . According to Gustafson et al., who measured  $p_{tc}CO_2$  as well as  $p_aCO_2$ , the  $CO_2$  increase was in fact 1.8mmHg/min, with a standard deviation of 0.35mmHg [3]. This correlated very well with our own findings in our pilot study (not published).

Using a non-inferiority design, a difference of means of 0.3mmHg/min, a standard deviation of 0.35mmHg/min, an alpha of 0.025 (one-sided) and a power of 80%, the necessary sample

size calculates to 22 patients per group. Therefore, we will include 25 patients in each group to account for possible drop outs. A value of 0.3mmHg/min would still only result in a difference in increase of 9mmHg in 30 minutes of apnoea time. We defined this as measurable, but still clinically acceptable, because the normal range of standard arterial pCO2 is 11mmHg (35-46 mmHg) [6].

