### **10.3 Planned Analyses**

#### **10.3.1 Datasets to be analysed, analysis populations**

Distribution of data will be checked using qq-plots and swilk command in stata, normal distributed data will be presented as means and standard deviation, otherwise median and interquartile range will be used. Proportions will be presented as numbers and percentage. Analytical statistics uses Mann-Whitney u-tests and Students t-test, according distribution, or ANOVA and Kruskal-Wallis for multiple groups. Each of the groups will a-priori be compared to the control group independently, without correction of multiple comparisons. Other multiple comparisons or subgroup-analyses will be performed using correction factors. Proportions will be compared by Chi-square tests or Fisher's exact test. As sensitivity analyses, we will do regression analyses, using mixed effects linear regressions.

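### The 80% power in section 10.2 belongs to one arm-versus-control comparison, while section 10.1 states a single null over all three arms and no success rule links the two

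*Protocol*

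**What the plan says.** The primary claim is stated in two places. The synopsis, under Objective(s), says: "Our primary hypothesis states that any of the three intervention is non-inferior to HFNCT regarding clearance of" CO2. Section 10.1 gives a single null, that the difference in mean ptcCO2 increase "between any of the three intervention groups and the control group is at least 0.3 mmHg/min, the control group being lower". The alternative there is that the difference "is less than 0.3 mmHg/min (non-inferior margin), one-sided testing".

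Section 10.2 gives one sample size calculation: a margin of 0.3 mmHg/min, an SD of 0.35 mmHg/min, and "an alpha of 0.025 (one-sided) and a power of 80%, the necessary sample" size is 22 per group, raised to 25 for drop-outs. It does not mention that there are three comparisons.

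Section 10.3.1, repeated in the synopsis, sets the testing rule: "Each of the groups will a-priori be compared to the control group independently, without correction of multiple comparisons". Other multiple comparisons and subgroup analyses are to be corrected.

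The protocol does not say whether success requires all three arms, any one arm, or is judged arm by arm.

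**The concern.** The hypothesis, alpha, power and multiplicity rule are all fixed in this protocol, so their fit can be judged without a separate analysis plan. The difficulty is the word 'any'. In the null of 10.1 it says that at least one arm is worse by the margin or more, and rejecting that means showing all three arms non-inferior. In the synopsis it can mean each arm or at least one arm. The three meanings carry different error rates and different power, and the protocol prints one alpha and one power without saying which meaning they serve.

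If two arms pass and one fails, the text does not settle whether the primary hypothesis was met, so that could be decided after the results are known. In a non-inferiority trial a false success means declaring a worse flow rate acceptable, and section 2.1.1 says a positive result could support wide use of lower-flow devices.

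**Working it through.** **Inputs.** Margin 0.3, SD 0.35, one-sided alpha 0.025, power 80% and 22 per group enlarged to 25 (section 10.2); one control shared by three equal-sized arms (sections 6.1 and 8.1). The true difference is not stated as an input. Zero is implied by the result and supported by the pilot in 10.1, described as a "small clinical pilot study that showed no differences regardless of flowrate or mouth opening".

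**1. Reproducing the plan's figure.** For one arm against control at true difference 0:

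n = 2(1.960 + 0.842)² × 0.35² / 0.3² = 21.4, so 22 per group.

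This matches. Power for that one comparison is 81% by the normal approximation and 79% by t test at n = 22, and 86% and 84% at n = 25. The 80% is therefore a per-comparison figure.

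**2. Power for all three arms.** With a shared control and equal groups, the three test statistics have pairwise correlation 0.5. At n = 22 the standard error of a difference is 0.35 × √(2/22) = 0.1055, so each statistic exceeds its critical value on average by 0.3/0.1055 − 1.960 = 0.883. At n = 25 the standard error is 0.0990 and the excess is 1.070. The probability that all three succeed is the trivariate normal probability at those values. It was checked by simulating t tests (400,000 runs):

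| Evaluable per group | One comparison (t) | All three (normal) | All three (t) |
|---|---|---|---|
| 22 | 79% | 63% | 60% |
| 25 | 84% | 71% | 68% |

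At exactly 80% per comparison, the all-three probability is 61%. The simple product 0.8³ = 51% does not apply, because the comparisons are positively correlated. By the normal approximation, 80% power for all three would need about 30 evaluable per group.

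**3. Type I error by reading.**
- All three must succeed: each test at 0.025 is enough and the overall error is at most 0.025. No correction is needed.
- Any one suffices: with all three arms exactly at the margin, P(at least one false claim) = 1 − P(all three Z < 1.960, correlation 0.5) = 6.3%; simulation gives 6.2% to 6.3%. The independence figure is 7.3%. The 6% is the worst case: with two arms at the margin and the third not tested there, the error from those two is about 4.5%, and with one it is 2.5%.

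**4. Sensitivity to the zero difference.** Section 10.2 also says that with the highest flow "and maximal mouth opening, there would be the least increase of" ptcCO2 per minute. Taking a small true disadvantage as an illustrative assumption, single-comparison power (t tests, n = 22 / 25) is 64% / 70% at 0.05 mmHg/min and 46% / 51% at 0.10. The protocol gives neither value. They show only that every power figure above depends on a true difference of zero.

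**The case against.** The best defence is that 'any of the three' simply means 'each'. Sections 10.1, 10.2 and 10.3.1 then agree: three separate questions, each tested at one-sided 0.025 with 80% power. The multiplicity sentence supports this, since it declares in advance that the groups are compared independently and reserves correction for other comparisons. Leaving separate arm-versus-control questions uncorrected is a defensible, disclosed choice. The German summary, which expects the lower flow rates in the plural not to be relevantly worse, also fits 'each' or 'all' better than 'one is enough', so the 6% figure rests on the least natural reading. This stands, and it is why the remedy is a restatement and not a redesign. It does not remove the point, because 10.1 writes one null and not three.

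A reader might infer more than the documents support:
- That alpha and power fit the hypothesis under no reading. The per-arm reading is coherent.
- That lost power and inflated error occur together. Under the all-three reading alpha holds and the uncorrected tests are the right procedure; under the any-one reading power for at least one success is about 95% at n = 22.
- That the trial falls 20 points short of its power. That uses 22 per group. The protocol enrols 25 and replaces patients excluded before the envelope is opened, so with all 25 evaluable the gap is 9 to 12 points. The protocol also never claims 80% for all three jointly.
- That section 10.2 contradicts itself on the zero difference. Its remark about the control can be read as explaining the choice of benchmark, and the pilot gives a basis for zero.

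**Conclusion.** The point holds as a mismatch between the stated hypothesis and the stated power, with no success rule to reconcile them. The 80% is correct for one comparison at zero true difference and SD 0.35. For the literal null of 10.1 the corresponding power is about 60% at 22 evaluable per group and 68% to 71% at 25, with alpha intact. If any single arm suffices, the family-wise error is up to about 6.2% against 2.5%. Only one of these applies, depending on the reading chosen. Under the per-arm reading neither is an error, but both should be disclosed. The figures assume normal data, equal SDs and equal evaluable numbers in all four groups.

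**What to change.** Rewrite section 10.1 and the synopsis objective as three separate hypotheses, one per experimental arm against control, each tested at one-sided 0.025. State that conclusions are drawn arm by arm and that no trial-wide claim is made unless all three arms succeed.

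Restate section 10.2 along these lines: 80% power for each single comparison at zero true difference; about 60% (22 per arm) to 68% (25 per arm) for all three. Add to section 10.3.1 that the uncorrected tests carry a family-wise error of up to about 6%.

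The cost is wording in four places and a less favourable joint power in print.

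Fixed-sequence testing, each step at 0.025, is an option for the sponsor if family-wise control is wanted without more patients, but it is not a required correction. At zero true difference its successive step powers are about 79%, 68% and 60% at n = 22, or 84%, 75% and 68% at n = 25, so whichever arm is placed last loses most. The documents do not support a particular order. Holding the family error at 2.5% by Bonferroni would instead need 29 evaluable per group for 80% per comparison; a Dunnett-type adjustment would need 28.

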#### **10.3.2 Safety analysis**

Incidences of side effects and other safety outcome variables will be compared with known results from the literature.

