| Background and Rationale: | 
After induction of general anaesthesia apnoea sets in. To ensure ventilation a tracheal intubation is then performed. If no measures to ensure ventilation are taken, desaturation will set in within minutes. To prolong the time to onset of desaturation pre-oxygenation is applied beforehand. Also, preparations to ensure swift tracheal intubation are made. Nevertheless, there is a phase, in which the patient is apnoeic, and deoxygenation may occur.
 
However, if anaesthesia needs to be provided in emergency situations or in the presence of a difficult airway, the rate of complication increases rapidly [1]. In these circumstances methods that reduce desaturation incidents during prolonged difficult intubation are desirable.
 
High-Flow nasal cannula therapy (HFNCT) is the administration of heated, humidified air/oxygen via nasal cannulas at rates of 50-100l/min. HFNCT was developed in intensive care unit as an alternative to continuous pressure support (CPAP). A new application for HFNCT in adults is the extension of apnoea time in patients with difficult airways who are undergoing general anaesthesia [2]. In this environment, a new term for this kind of oxygen therapy was created: THRIVE - transnasal humidified rapid-insufflation ventilatory exchange. Using HFNCT with continuous laryngoscopy, Patel et al. [2] demonstrated in fact a ventilatory effect with HFNCT.
 
THRIVE is thought to have a ventilatory effect, because slower than expected increase in <math>p\text{CO}_2</math> has been described [2, 3]. In these studies, researches compared their data to studies from the 1950-ies, where <math>\text{CO}_2</math> increase during apnoea was investigated [4, 5]. However, technology as well as patient factors have changed since then, and no study has ever directly compared different flow rates and the effect on <math>\text{CO}_2</math> clearance. Our previous research showed, that the claimed ventilatory effect is absent in children (Riva et al., British Journal of Anaesthesia, 2018, in press). Therefore, we want to systematically examine the <math>\text{CO}_2</math> clearance and possible influences in adults, and to determine, if a ventilatory effect is present at all.
 
This study investigates under controlled circumstances the concept of THRIVE to prolong the apnoea time without deoxygenation and to improve safety of airway management in patients. Furthermore, this study enables to quantify the physiologic effects of different flow rates of oxygen on carbon dioxide elimination in apnoeic patients as well as the effect of elevated <math>\text{CO}_2</math> levels on cerebral perfusion and other vital parameters.
 |

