## 5.3 Safety Outcomes

Arterial blood gas analysis will be conducted every two minutes to detect severe acidosis (pH <7.10) or hyperkalaemia (>6.0 mmol/l).

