According to randomization, the intervention will be applied. If jaw thrust is performed, upper airway patency will be visually confirmed using nasopharyngeal fiberscope (EF-N slim, Acutronic, Hirzel, Switzerland). In most cases this should be the case [18]. If not, an oropharyngeal airway (Guedel) will be inserted, and if necessary, manual assistance performed to obtain the required result. If, despite these interventions, the airway is not patent, the study will end prematurely (drop-out). This is very unlikely to happen.

After confirmation of upper airway patency, the experiment will be continued until one of the following criteria is met: SpO2 < 92%, ptcCO2 > 80 mmHg, pH < 7.1, K > 6.0 mmol/l or apnoea-time > 15 minutes.

During the intervention, we will continuously measure arterial blood pressure, pulse oximetry, ptcCO2, ptcO2, heart rate, depth of anaesthesia (Narcotrend™), brain oxygenation, cardiac output by pulse contour analysis, and ventilation distribution changes by thoracic electrical impedance tomography (EIT). Latter will be measured with a PulmoVista® 500, by Dräger, Lübeck, Germany. Furthermore, we will take arterial blood samples at the onset of apnoea, one minute after apnoea, and thereafter every two minutes to perform blood gas analysis (total of max. 10 measurements).

During the experiment, one anaesthesia staff member will be free of all study related responsibilities in order to ensure the patient's wellbeing during anaesthesia consisting of stable blood pressure, neuromuscular blockage, and anaesthesia depth.

The experiment stops, if one of the following criteria is met: SpO2<92%, ptcCO2>80 mmHg, pH<7.1, K>6.0 mmol/l, t >15 minutes. Thereafter the airway will be secured in the planned manner and anaesthesia will continue without any further interruptions.

Patients will be visited before discharge on the first postoperative day or contacted by phone, and asked for any sort of pain (throat, mandibular joint, head, etc.), nausea, vomiting, nasal dryness, lip injuries, dental damages, other injuries, or any other discomfort or complication using a (modified) visual analogue scale (VAS), where 0 is no pain (or discomfort), and 10 is maximum pain (or discomfort) where applicable. We will also assess all kinds of injuries obtained during anaesthesia.

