Overall, we will include 100 patients, 25 per group. Patients will be blinded as to their group allocations. Double-blinding is not possible, as devices differ from each other.

This design allows us to focus our study on the primary outcome, since we ensure, that free air circulation (and possible CO2 clearance) is possible by visually assessing airway patency. Through measurement of extended vital parameters, we can identify physiologic influence of rising CO2 in anaesthetized patients undergoing apnoeic oxygenation.

In addition, demographic data will be extracted from the AIS. This only includes standard data, that is collected through routine normal clinical workflow, such as age, sex, weight, height, BMI, airway risk factors, underlying diseases, smoking habits, ASA physical health status and indication for the surgery.

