#### 8.5.3.1 Adverse events

Any adverse events during the study period will be recorded.

An **Adverse Event (AE)** is any untoward medical occurrence in a patient or a clinical investigation participant administered a pharmaceutical product, and which does not necessarily have a causal relationship with the study procedure. An AE can therefore be any unfavourable and unintended sign (including an abnormal laboratory finding), symptom, or disease temporally associated with the use of a medicinal (investigational) product, whether or not related to the medicinal (investigational) product. [ICH E6 1.2]

A **Serious Adverse Event (SAE)** is classified as any untoward medical occurrence that:

- results in death
- is life-threatening
- requires in-patient hospitalization or prolongation of existing hospitalisation
- results in persistent or significant disability/incapacity
- is a congenital anomaly/birth defect

In addition, important medical events that may not be immediately life-threatening or result in death, or require hospitalisation, but may jeopardise the patient or may require intervention to prevent one of the other outcomes listed above should also usually be considered serious. [ICH E2A].

All SAEs will be reported immediately and within a maximum of 24 hours to the Sponsor-Investigator of the study.

SAEs resulting in death are reported to the local Ethics Committee within 15 days.

SUSARs will be reported to the local Ethics Committee within 15 days.

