## 8.6 Procedures at each visit

First visit during pre-anaesthesia visit to rule out exclusion criteria and to obtain written informed consent and to complete any missing data from the pre-operative interview. A follow-up visit will be performed (structured post-medication interview) before discharge. This includes asking for possible side effects: sore throat/nose, mandibular pain, nausea, dental damages, oropharyngeal injuries of any kind, headaches as well as nasal dryness.

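### The safety analysis section names the literature, not the concurrent randomised control arm, as comparator for side effects, so the comparator is at best ambiguous

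*Protocol*

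**What the plan says.** Section 10.3.2 of the protocol, the only text given over to safety analysis, reads in full: "Incidences of side effects and other safety outcome variables will be compared with known results from the literature". It names no source, no reference rate and no other comparator.

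The trial has an internal comparator. Four groups are randomised, one of them the control (70 l/min with continuous laryngoscopy), and section 6.1 fixes the numbers: "Overall, we will include 100 patients, 25 per group".

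Section 10.3.1 gives a general rule: "Each of the groups will a-priori be compared to the control group independently, without correction of multiple comparisons". It adds chi-square or Fisher tests for proportions. Neither statement names safety or side effects, and neither excludes them.

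The data in question are:
- the postoperative interview: in 6.1, pain and "nausea, vomiting, nasal dryness, lip injuries, dental damages, other injuries, or any other discomfort or complication"; in 8.6, "asking for possible side effects: sore throat/nose, mandibular pain, nausea, dental damages" and further items;
- adverse events (8.5.3.1): "Any adverse events during the study period will be recorded";
- the safety outcomes (5.3): blood gases every two minutes "to detect severe acidosis (pH <7.10) or hyperkalaemia (>6.0 mmol/l").

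**The concern.** The arms differ in ways that could plausibly change the side effects being asked about. Control patients have a videolaryngoscope in place throughout apnoea, while the other three arms have jaw thrust. Flow is 70, 10 or 2 l/min, and according to section 3.6 heated oxygen goes to the high-flow patients. Sore throat, jaw pain, lip and dental injury and nasal dryness are natural candidates for a difference between arms. Section 2.1.1 also hopes that showing non-inferiority of lower flows will make care safer through wider availability, so a reader will want to know how side effects compare between techniques.

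A published incidence cannot answer that. It mixes the effect of the technique with differences in patients, surgery and the way side effects were elicited. The protocol applies similar reasoning elsewhere: the synopsis objects to judging carbon dioxide clearance against data from the 1950s, saying "However, technology as well as patient factors have changed since then". With no reference rate fixed in advance, the benchmark could also be chosen after the results are known.

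At stake is the interpretability of secondary safety reporting.

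**Working it through.** **1. Which items depend on 10.3.2**

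| Item | Route to a by-arm comparison apart from 10.3.2 |
|---|---|
| Not tolerating 15 minutes of apnoea | Yes: between-group hypothesis in 10.1 |
| Arterial pH | Yes: secondary outcome in 5.2 |
| Potassium as a continuous value | Probably: the synopsis lists blood gas parameters among secondary outcomes |
| VAS scores | Probably: they are scores, not incidences, and fit the t-test or Mann-Whitney rule in 10.3.1 |
| Interview incidences | Only if 10.3.1 is read to include them |
| Adverse events | Only if 10.3.1 is read to include them |
| Count of potassium >6.0 mmol/l | Only if 10.3.1 is read to include it |

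The point concerns the last three rows.

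**2. The plan's own figure: where 25 per arm comes from**

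Inputs from 10.2: margin 0.3 mmHg/min, SD 0.35 mmHg/min, one-sided alpha 0.025, power 80%, true difference 0.

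n = 2 × [0.35 × (1.960 + 0.842) / 0.3]² = 21.4, rounded up to 22 per group. This reproduces the stated 22, raised to 25 for drop-outs. The size was set for the carbon dioxide slope, not for side effects.

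**3. What the control arm can deliver for safety**

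The protocol gives no side-effect rates, so the counts below are assumptions. Newcombe's interval combines the Wilson limits (l, u) of the two proportions:

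- lower = d − √[(p₁ − l₁)² + (u₂ − p₂)²]
- upper = d + √[(u₁ − p₁)² + (p₂ − l₂)²]

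For 5/25 against 10/25, the Wilson limits are 0.089 to 0.391 and 0.234 to 0.593, and d = −0.200.

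- lower = −0.200 − √(0.111² + 0.193²) = −0.422
- upper = −0.200 + √(0.191² + 0.166²) = 0.053

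| Intervention v control | Difference, points | 95% CI |
|---|---|---|
| 5/25 v 10/25 | −20 | −42 to 5 |
| 5/25 v 13/25 | −32 | −53 to −5 |
| 5/25 v 0/25 | 20 | 3 to 39 |
| 2/25 v 0/25 | 8 | −7 to 25 |
| 0/25 v 0/25 | 0 | −13 to 13 |

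Exact Fisher power (two-sided 0.05) is 23% for 20% against 40%, and 79% for 20% against 60%. The by-arm comparison is therefore descriptive.

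**4. What the literature comparison delivers for the same question**

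Its error as an estimate of intervention minus control is (control rate) − (published rate). Assume 20% in an intervention arm and 40% in control, a true difference of −20 points:

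| Published rate | Apparent difference | Error, points |
|---|---|---|
| 20% | 0 | +20 |
| 30% | −10 | +10 |
| 40% | −20 | 0 |
| 50% | −30 | −10 |

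More patients would not reduce this error.

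Now assume no difference between arms and a published rate of 20%. A two-sided exact binomial test of one arm of 25 against 20% rejects at 0 or 1 events and at 10 or more.

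| True rate in every arm | False signal, one arm v 20% | False signal, Fisher v control |
|---|---|---|
| 30% | 19% | 2% |
| 40% | 58% | 3% |

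**The case against.** The strongest reply is that 10.3.2 does not exclude the control arm. It follows directly on a general rule that compares each group with control and is not limited to efficacy. Read together, 10.3.1 supplies the by-arm comparison and 10.3.2 adds an external one. This reading is possible and stands. A reader might infer that the protocol forgoes any between-arm safety comparison. The documents do not support that, and the first two rows of the item table contradict it directly. What remains is that the section headed safety analysis names a different comparator from the general rule, and nothing says which governs side effects. That safety tables by arm are not described is not itself a finding, because such detail can sit in an analysis plan.

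Second, the literature comparison has a use that the control arm lacks. Section 3.5 states that high-flow nasal oxygen is not standard of care at anaesthesia induction, where apnoea is kept as short as possible. All four arms undergo study apnoea of up to 15 minutes, so arm against control cannot show whether the study procedure as a whole adds side effects to routine anaesthesia. This also stands, and it is a reason to keep the comparison with its purpose stated.

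Third, a reader might infer that randomisation removes every difference that burdens a literature comparison. It does not. It balances patient selection and type of surgery in expectation. The airway is secured after the intervention and could differ by arm, since control patients have just had laryngoscopy. Patients are blinded, but section 6.3 calls the study open and no blinding of the interviewer is stated. A common interview makes ascertainment more alike than against published series, but does not guarantee it.

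Finally, the synopsis criticism concerns old carbon dioxide data, so it supports the argument by analogy only.

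**Conclusion.** The point holds in limited form. Section 10.3.2 leaves the comparator for interview incidences, adverse events and the count of potassium above 6.0 mmol/l ambiguous. If it is followed alone, the comparator is the weaker one for questions about flow rate and laryngoscopy versus jaw thrust.

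The size cannot be taken from the protocol. Under the assumed rates above, the error of the literature comparison ranges from −10 to +20 points and is zero when the published rate happens to match control. The by-arm comparison avoids this offset but is imprecise, with intervals of 13 points either side even when no events occur in either arm. It supports description, not proof.

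This is a low-priority, essentially free improvement. The primary non-inferiority conclusion is unaffected.

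**What to change.** Replace the sentence in 10.3.2 with:

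*Side effects, adverse events and the safety outcomes in 5.3 will be reported by randomised arm, and each intervention arm will be compared with control as a risk difference with a 95% confidence interval (Newcombe), descriptively. Rates will in addition be set against published rates for routine anaesthesia, to judge the study apnoea procedure as a whole.*

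The cost is two sentences. The interview, adverse-event records and blood gases are already planned for every arm. No extra patients or measurements are needed, and the primary analysis does not change.
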